### Primary outcome and its assessment

A positive primary outcome of this study will be an increase of at least four points in the Alzheimer’s Disease Assessment Scale-cognitive subscale (ADAD-cog) [27] total score; this is considered to be a clinically meaningful increase [28]. Total scores of the ADAD-cog, Chinese version of Mini-Mental State Examination (C-MMSE) [29,30] and Chinese version of Disability assessment for dementia (C-DAD) score [31] will be used as secondary outcomes.

Outcome measurements will be carried out during the study visits at weeks 0, 12 (half of treatment), 24 (end of treatment) and 30 (end of observation period). Safety assessment, which includes reporting of adverse events (AEs), measurement of vital signs and physical examination, will be carried out throughout the study. In addition, laboratory safety screening of liver and renal function will be performed at week 24. Bilingual assessors, trained by the same neurology specialist [name] and clinical psychologist [name], will be blind to the treatment allocation.

Clinical assessment will be rescheduled within 7 days after the scheduled clinical visit in case of any unexpected condition such as severe weather conditions. Phone call reminders will be given to the caregivers one day before the days of assessment.

A home diary will be given to each study participant’s caregiver to record treatment and changes in the participant’s medical condition. Formal instruction for the home diary will be given during the first visit. Revision and checking of the diary will be carried out with the caregiver during each formal visit by the assessors. Compliance in taking the treatments will be determined by the record of the diary and the number of the returned medicine/placebo packages.

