**Methods/Design:**

This study will be a double-blind, randomized, placebo-controlled, add-on trial. After a 2-week run-in period, eligible patients with mild to moderate AD will be recruited and given either DTD or placebo twice daily for 24 weeks with follow-up 6 weeks after the last treatment. An increase of four points or greater on the scores of Alzheimer’s Disease Assessment Scale-cognitive subscale (ADAD-cog) will be considered as a positive primary outcome. Total scores of the ADAD-cog, the Chinese version of Mini-Mental State Examination (C-MMSE), and the Chinese version of the Disability Assessment for Dementia (C-DAD) score will be used as secondary outcomes. Adverse events will also be reported.

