### Statistical analysis

The proportion of patients with at least a four-point change in ADAS-cog and MMSE and the scores on C-DAD will be compared between the active treatment and placebo groups using the Chi-Squared test and independent sample t test, respectively. Missing data will be input using the last-observation-carried-forward (LOFC) approach. All patients randomized with at least one post-randomization measurement will be included in the primary analysis to follow the intention-to-treat principle. Analyses will be done with SPSS 19.0 package (SPSS, Chicago, IL).

To get a more comprehensive picture of the efficacy of DTD, a post-hoc analysis of the differences in the change of ADAS-cog and C-DAD sub-scores of the active treatment group will be compared between the active and placebo groups. To reduce the number of statistical comparisons, analyses will be performed with a hierarchical approach. To begin, the scores of ADAS-cog at week 24 (end of treatment) for the active treatment and placebo groups will be compared. If the difference is deemed statistically significant at a 2-sided *α*-level of 0.05, the scores of ADAS-cog at week 12 (half of treatment) and week 30 (end of observation period, that is, without treatment) will be compared between groups. C-DAD will be analyzed in the same manner as ADAS-cog.

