### Compliance strategy

This will be a 30-week clinical trial, in which subjects will need to take study medication for 24 weeks with 8 regular visits (week 0, 4, 8, 12, 16, 20, 24 and 30). In order to maximize subjects’ compliance, first, we will have a thorough consent process for all participants; we will explain in detail the study schedule, potential side effects of treatment, and the responsibilities of the subjects. Second, we will screen potential subjects carefully during a 2-week run-in period in order to exclude ineligible patients or patients who are unlikely to comply with treatment regimen before randomization. Third, we will try to prevent dropouts by providing ongoing support to patients. A special e-mail account and a direct telephone line set up for this clinical trial will enable the study team to personally communicate with the patients. An information sheet will be given to each participant providing them and their caregivers with means of urgent contact. Extra visits and free medical care will be arranged for any participant who feels harmed by the trial protocol. Fourth, this is an add-on design [32], which means that the study treatment is added to their existing treatment. Certainly those participants receiving the placebo should not experience any difference in their condition, while those receiving the DTD should improve or at least remain the same.

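### The primary outcome counts a rise of at least four ADAS-cog points as positive, but a rise on that scale is deterioration, and the statistical analysis section does not correct the direction

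*Protocol article*

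**What the plan says.** The section on the primary outcome and its assessment reads: "A positive primary outcome of this study will be an increase of at least four points" in the ADAS-cog total score (the article also spells it ADAD-cog). It adds that "this is considered to be a clinically meaningful increase". The Methods/Design paragraph of the abstract gives the same direction: "An increase of four points or greater on the scores of" the scale "will be considered as a positive primary outcome". Total scores of ADAS-cog, C-MMSE and C-DAD are named as secondary outcomes.

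The statistical analysis section describes the comparison differently: "The proportion of patients with at least a four-point change in ADAS-cog and MMSE and the scores on C-DAD will be compared" between the arms, "using the Chi-Squared test and independent sample t test, respectively". It gives the four-point change no direction. Its second paragraph compares ADAS-cog scores at week 24 first, two-sided at 0.05, and goes on to weeks 12 and 30 only if week 24 is significant.

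The compliance section shows which result is hoped for: patients on placebo should notice no difference, "while those receiving the DTD should improve or at least remain the same".

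**The concern.** A higher ADAS-cog total means more errors and worse cognition. A rise of four points is therefore a decline, and the written rule labels it a positive outcome. The word increase appears in both the abstract and the methods, and the methods repeat it when justifying the threshold, so this is not one stray word. The article nowhere says that the scale is reverse-scored or that change is computed as baseline minus follow-up. Either statement would rescue the wording.

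If the rule is programmed as it stands, an effective treatment yields fewer positive patients than placebo, and the primary result carries the wrong sign. The trial is also meant to supply sample-size information for a full-scale study, and responder rates taken in the wrong direction would be passed on to that planning.

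The analysis section does not settle the matter. One undirected phrase covers ADAS-cog, where improvement is a fall, and MMSE, where improvement is a rise. Read literally, it would count improvers and decliners together.

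**Working it through.** **The statements side by side**

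| Place in the article | Rule | Direction |
|---|---|---|
| Abstract, Methods/Design | at least 4 points on ADAS-cog is positive | increase |
| Primary outcome and its assessment | at least 4 points on ADAS-cog total is positive | increase |
| Statistical analysis | at least 4 points on ADAS-cog and MMSE | none |
| Compliance strategy | expected course on DTD | improve or remain the same |

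The last row shows that improvement is meant. On an error score the first two rows count the opposite, and the third does not isolate improvement.

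**Inputs for the illustration.** From the article: the threshold of 4 points and the planned 20 patients per arm. The article has no sample size calculation and gives no effect, SD or responder rate, so there is no stated figure to reproduce. Assumed: change from baseline is normal, a higher score is worse, mean change m is +1.5 on placebo and -1.5 on DTD (a true benefit of 3 points), and SD is 6.

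**Formulas**
- Increase of at least 4: 1 - Φ((4 - m)/SD)
- Decrease of at least 4: Φ((-4 - m)/SD)
- Either direction: the sum of the two

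**Increase rule, as written**
- Placebo: 1 - Φ(2.5/6) = 1 - Φ(0.417) = 33.8%
- DTD: 1 - Φ(5.5/6) = 1 - Φ(0.917) = 18.0%

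**Decrease rule**
- Placebo: Φ(-5.5/6) = 18.0%
- DTD: Φ(-2.5/6) = 33.8%

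**Undirected rule**
- Placebo: 33.8% + 18.0% = 51.8%
- DTD: 18.0% + 33.8% = 51.8%

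With these rates and 20 patients per arm, exact binomial calculation gives placebo more positive patients than DTD under the increase rule with probability 0.838. It is 0.876 at SD 5 and 0.802 at SD 7.

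**Other assumed means.** The equality of the undirected rates comes from placing the two means symmetrically about zero. DTD-minus-placebo differences, in percentage points:

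| Placebo / DTD mean, SD | Increase rule | Decrease rule | Undirected rule |
|---|---|---|---|
| +1.5 / -1.5, SD 6 | -15.9 | +15.9 | 0 |
| +1 / -1, SD 7 | -9.7 | +9.7 | 0 |
| +1 / -3, SD 5 | -19.3 | +26.2 | +6.9 |
| +1 / -3, SD 7 | -17.5 | +20.6 | +3.0 |
| +3 / 0, SD 5 | -20.9 | +13.1 | -7.8 |

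In every row the increase rule favours placebo although DTD is truly better. The undirected difference is between 0 and about 8 points in size, and its sign depends on the means.

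**The case against.** The strongest reply is that the intent is plain. The article calls the four points clinically meaningful and expects DTD patients to improve or remain the same, so a sensible analyst would code improvement. Raw scores are kept, the responder flag is derived later, and the two-sided comparison of total scores does not depend on the word. All of this stands: the error is in a definition and has not damaged any data. It does not remove the point, because the responder rule is the primary outcome, the total scores are secondary, and the stated direction is wrong in both places that define the outcome. This is a wrong statement, not a detail that an article leaves to a fuller document.

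It is also fair to say that the scoring direction of ADAS-cog appears nowhere in the article. The point rests on a basic property of the scale it names.

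Three stronger readings are tempting, and the article does not support them:
- **That the plan holds two rival primary rules.** The sentence in the analysis section is better read as an ambiguous restatement covering two scales that run in opposite directions.
- **That an undirected rule always wipes out a real effect.** Exact cancellation needs means symmetric about zero.
- **That the lack of a named week for the responder rule inflates the false-positive rate across three visits.** This assumes free choice among weeks 12, 24 and 30. The article tests scores at week 24 first, and although that order is written for scores rather than for the responder rule, the week is a detail an article may leave to the full plan.

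**Conclusion.** The primary outcome is wrong as written. The abstract and the methods count a rise of at least four points on an error score as success, which contradicts the article's own expectation for DTD, and the analysis section leaves the direction open. A reader might infer that deterioration was deliberately chosen as the endpoint, or that the reported result must come out reversed. Neither follows: improvement is almost certainly meant, and the sign reverses only if the words are applied literally.

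The conclusion about direction needs only the scoring of the scale. Its size rests on assumed inputs: with means of +1.5 and -1.5 and SD 6, the rule turns an advantage of 15.9 points for DTD into a disadvantage of 15.9 points. An undirected count would lose most of the contrast in most of the cases examined, and all of it only under symmetric means. With assumed means of +3 and 0 it would point the wrong way.

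**What to change.** Before unblinding, use one definition in the abstract, the primary outcome section and the statistical analysis section: a responder is a patient whose ADAS-cog total decreases (improves) by at least 4 points from week 0 to week 24. Week 24 is the end of treatment and the time point the analysis section already tests first for scores. Change the remark on clinical meaning to match. If a C-MMSE responder rule is kept, write it separately with its own direction (increase) and label it secondary.

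The cost is an amendment to the wording, submitted to the Ethics Committee as the article requires for any amendment, and a check that the registry entry agrees. It needs no extra patients, visits or procedures. The article reports 36 subjects so far with the study still ongoing, and masking until the end of the study, so on the article's account the change can still be made blind.

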### Recruitment procedures

Three methods will be used to recruit participants with AD. The first source of candidates will be referral from two public Western medicine hospitals in Hong Kong (Prince of Wales Hospital and Queen Elizabeth Hospital) from our co-investigator (Co-I), [name], and our research teammate, [name]. The second source will be referral from the Chinese medicine clinic of Hong Kong Baptist University. A third source of candidates will be those who respond to advertisements published in local newspapers and newsletters of local AD societies.

Figure 1 shows the schedule of enrollment. We plan to recruit at least 40 patients, which will allow 20 for the DTD group and 20 for the placebo group in this study. All patients diagnosed with AD will be referred to a Chinese medicine doctor who is the Principle Investigator of the study ([name]), or to a Research Assistant ([name]), for further assessment and recruitment. The aim, procedures, nature of study and possible side effects of DTD will be explained by the PI or RA; then, each subject will be asked to sign a written consent [see Additional file 4] to take part in the study. Patients will be informed that they are free to withdraw at any time during the study.

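### The four-point ADAS-cog responder is an inefficient primary analysis at about 20 per arm, and the continuous ADAS-cog comparison that the plan describes has no baseline adjustment

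*Protocol article*

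**What the plan says.** The Primary outcome section sets a responder rule on the ADAS-cog total, "A positive primary outcome of this study will be an increase of at least four points", and gives its reason: "this is considered to be a clinically meaningful increase". The full score is a secondary outcome ("Total scores of the ADAD-cog, Chinese version of Mini-Mental State Examination (C-MMSE" and the C-DAD score are listed there). ADAS-cog is measured at weeks 0, 12, 24 and 30.

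The Statistical analysis section compares "The proportion of patients with at least a four-point change in ADAS-cog and MMSE" between arms by chi-squared and keeps the independent-samples t test for C-DAD scores. A separate paragraph, introduced as "a post-hoc analysis of the differences in the change of ADAS-cog and C-DAD sub-scores", sets out a stepwise procedure: "To begin, the scores of ADAS-cog at week 24 (end of treatment) for the active treatment and placebo groups will be compared". Weeks 12 and 30 are compared only if that result is significant at two-sided 0.05. No baseline adjustment is mentioned.

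On size, the Recruitment procedures section says: "We plan to recruit at least 40 patients, which will allow 20 for the DTD group and 20 for the placebo group". The Discussion says that a sample size calculation does not apply and that no earlier data exist from which to size an ADAS-cog effect.

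**The concern.** A cut at four points treats a patient who changes by 4 like one who changes by 12, and a patient who changes by 3 like one who worsens. In a trial of about 40 patients that discarded information is costly. The Discussion itself names sample size as the feature that could undermine the study's value.

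The continuous comparison has a related weakness. A raw week-24 score carries all the spread between patients that was already there at entry. The week-0 score removes much of that spread, and it is collected anyway.

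At stake is how much this pilot can say about whether DTD has an effect, and how precisely it estimates that effect for the full trial it is meant to inform.

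**Working it through.** **Nothing to reproduce.** The article gives no power, SD, effect or responder rate.

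**Inputs from the article:** 20 per arm, 1:1 allocation, and a four-point cut. Two-sided 0.05 is stated for the week-24 comparison and assumed for the responder test.

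**Assumed:** normal change scores, counted in the direction of improvement; SD of change 5 to 8; placebo mean change -1 to +1; true difference 3 or 4 points; no dropout.

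**Step 1, responder rates.** p = 1 − Φ((4 − mean)/SD). With SD 6, placebo mean 0 and a difference of 4 points:
- placebo: 1 − Φ(4/6) = 25.2%
- DTD: 1 − Φ(0) = 50.0%

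**Step 2, power for the same patients.** The responder test is the uncorrected Pearson chi-squared, by exact binomial enumeration. The change score uses the noncentral t with 38 df and noncentrality (difference/SD)·√(20/2). In the central case these give 36.8% and 53.8%, a relative loss of 1 − 36.8/53.8 = 32%, or 17 percentage points. Ranges below run over the placebo mean.

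| Difference | SD of change | Responder | Change-score t test |
|---|---|---|---|
| 3 | 5 | 28-31% | 46% |
| 3 | 6 | 22-23% | 34% |
| 3 | 7 | 18% | 26% |
| 3 | 8 | 14-15% | 21% |
| 4 | 6 | 36-37% | 54% |

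Over SD 5 to 8, differences of 3 to 4 points and placebo means of -1 to +1, the relative loss is 28-39%. On a wider grid (differences 2 to 6, placebo mean -2 to +1) it is 14-46%. It is smallest at very large effects (about 14% at a standardised difference of 1.2) and largest when few placebo patients reach the cut.

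**Step 3, the same loss as sample size.** For 80% power in the central case, the change score needs 2·(1.96 + 0.84)²·6²/4² ≈ 35.3, so 36 per arm. The responder comparison (25.2% against 50.0%) needs 59 per arm.

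**Step 4, the week-24 comparison as worded.** The article names no test for it, so a two-sample t test on raw scores is taken. Assume a score SD of 10 at both visits, a change SD of 6 and a difference of 4 points.
- Unadjusted: standardised difference 4/10 = 0.40; power about 23%.
- Correlation between visits: 1 − 6²/(2·10²) = 0.82.
- Residual SD after baseline adjustment: 10·√(1 − 0.82²) = 5.72.
- Adjusted: standardised difference 4/5.72 = 0.70; power about 58% (37 df).

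The 23% lies below the responder's 37% and depends on the assumed score SD. At a score SD of 8 the unadjusted power is 34% (4/8 = 0.5), still slightly below. At 7 it is 42%, above.

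**The case against.** The strongest reply is that this is a legitimate design preference. The four-point rule has a stated clinical rationale, the study calls itself a pilot, it claims no power, and it says its evidence will be weak even if positive. No stated figure is wrong. All of that stands, and it is why the point concerns efficiency and not an error. Even the best alternative in the central case stays below 60% power.

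A second reply is that the article condenses a fuller plan that may specify an adjusted model. That is possible. The point rests on what the article does state: a dichotomised primary, and a comparison worded as scores at week 24.

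Three stronger readings are tempting, and the article does not support them.
- **That the change score already opens the stepwise procedure.** The first step is worded as week-24 scores. The word change appears only in the sentence introducing that paragraph. The efficiency gain belongs to a change or baseline-adjusted analysis, not to that step as written.
- **That the plan has two competing lead analyses.** One primary outcome is named, total scores are listed as secondary, and the stepwise procedure sits in a paragraph labelled post-hoc. Its first step decides only whether weeks 12 and 30 are compared.
- **That the mean difference and SD for sizing the full trial would be lost.** The total score is a declared secondary outcome, so both can be obtained whichever analysis is called primary.

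Finally, a late change of primary outcome invites suspicion of outcome switching. The absence of interim analyses does not prove that nobody has seen pooled scores. That cost is real.

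**Conclusion.** The point holds as one of inefficiency. With 20 per arm and moderate effects, the responder test gives up roughly 28-39% of the power of a change-score t test (14-46% across the wider grid). The continuous comparison, as worded, may be weaker than the responder itself: about 23%, against about 58% with baseline adjustment, at a score SD of 10, change SD of 6 and a 4-point difference. A relative loss appears throughout the grid examined, but its size rests on assumed SDs, effects and normality, none of which the article supplies. The case for adjusting the week-24 comparison for baseline stands on its own. The case for changing the primary outcome is sound but must be weighed against the late stage of recruitment.

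**What to change.** **Minimum change.** In the Statistical analysis section, analyse week-24 ADAS-cog with a linear model containing treatment and baseline ADAS-cog, and report the adjusted mean difference with a 95% CI. This needs no new data or visits, only revised wording.

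**Preferred change.** Make that analysis the primary one in the Abstract, the Primary outcome section and the Statistical analysis section. Keep the proportion improving by at least four points at week 24 as a secondary responder summary, so that the clinical rationale is still served.

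**Cost.** The preferred change needs ethics approval of an amendment (required under Study design) and a registry update. It alters the primary outcome of a registered trial when the Trial status section already reports 36 subjects against a plan of at least 40. It should therefore be dated before unblinding, state what outcome data anyone had seen by then, and be reported openly with the original primary result alongside. If the sponsor judges that cost too high, the minimum change is still worth making.

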### Study medication

The herbal medicine under study is DTD (Table 1). It is composed of Arisaema Cum Bile (DanNanXing in Chinese), Pinelliae Rhizoma (FaBanXia in Chinese), Aurantii Immaturus Fructus (ZhiShi in Chinese), Poria (FuLing in Chinese), Citri Reticulatae Pericarpium (ChenPi in Chinese), Acori Tatarinowii Rhizoma (ShiChangPu in Chinese), Ginseng Radix (RenShen in Chinese), Bambusae in Taeniam Caulis (ZhuRu in Chinese), Glycyrrhizae Radix (GanCao in Chinese), Zingiberis Recens Rhizoma (ShengJiang in Chinese) and dextin [13]. The test report of the DTD quality control is attached in the Additional file 3. The placebo is made of caramel (2%), gardenia yellow pigment (0.05%), sunset yellow (0.02%), tartrazine (0.02%), dextrin (95%) and broadleaf holly leaf (2.91%) [25]. The granules were produced in a single batch (DTD batch no.: A12074 Placebo batch no.: A120817) strictly in compliance with standards of Good Manufactory Practice (GMP) and Chinese Pharmacopoeia 2010 to ensure the stability and homogeneity of the composition as produced by PuraPharm Pharmaceuticals Company Limited. The chemical compositions of the final products were analyzed for contamination with heavy metals, toxic elements, microbe and pesticide residues; both final products were analyzed for stability and adherence to quality standards. The active treatment granules and the placebo granules have identical appearance and smell, and both have been packed in sealed opaque aluminum sachets and put in zip lock bags (10 sachets each). Only the treatment code is printed on the package to ensure successful blinding of patients [26]. One sachet contains 13.5 g, a dosage equivalent to 67.5 g herbs. All herbal and placebo granules will be distributed by [name] with both written and verbal instructions for each participant. Patients will be instructed to take the granules orally by dissolving a sachet of granules in 150 ml hot water, stirring well, then drinking the solution, two times per day, at least two hours apart from taking any routine Western medication. Patients will be allowed to discontinue the study granules temporarily if any adverse events occur. Patients will be instructed to report such events to a special e-mail account or by a direct telephone line. Additional treatments for a newly occurring illness, for example, flu or diarrhea, or adverse event during the study will be allowed but must be reported to the assessor.

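### The assessors who are to be blind, and who appear to be the outcome raters, also check the caregiver diary at every visit and are told of added treatments, so information that can suggest the arm reaches them

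*Protocol article*

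**What the plan says.** Under *Primary outcome and its assessment*, the Protocol article says that the assessors "will be blind to the treatment allocation". In the same section, the caregiver keeps a home diary "to record treatment and changes in the participant’s medical condition", and "Revision and checking of the diary will be carried out with the caregiver during each formal visit by the assessors". Compliance is judged from the diary and from the count of returned packages.

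The same section fixes the outcome visits: "Outcome measurements will be carried out during the study visits at weeks 0, 12 (half of treatment), 24 (end of treatment) and 30". *Compliance strategy* lists "8 regular visits (week 0, 4, 8, 12, 16, 20, 24 and 30".

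Under *Study medication*, patients may interrupt the granules temporarily if an adverse event occurs. They report events to an e-mail account or a telephone line. The next sentence concerns additional treatments for a newly occurring illness "or adverse event during the study will be allowed but must be reported to the assessor". That section also says that the two products have identical appearance and smell and that only a treatment code is on the package.

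**The concern.** Blinding of raters protects the comparison only if they do not learn, from elsewhere, things that point to the arm. Here the people named as blind are also given the running account of each patient's course: whether granules were taken or interrupted, how the caregiver thinks the patient is doing, and which added treatments were needed. Being told of a treatment for an adverse event discloses the event.

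The protocol itself supplies a reason to guess from such information. *Compliance strategy* states the expectation that placebo patients will notice no difference, while DTD patients will improve or at least hold steady. An assessor who shares that expectation and reads of improvement or decline has grounds for a guess. A ten-herb product against a placebo that is 95% dextrin could also be tolerated differently, although the article gives no side-effect profile for DTD.

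If a guess shifts judgement-based items, and is right more often than chance, the shift goes with treatment and counts as efficacy. The primary outcome is a four-point threshold on a rated scale in a small trial, so a few patients near the threshold matter.

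**Working it through.** The article gives no standard deviation, effect size or power, so there is no figure of its own to reproduce. The check has two parts: the overlap of tasks, then an illustration of size.

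**1. Overlap of tasks**

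| Item | Article says | Section |
|---|---|---|
| Who is blind | The assessors | Primary outcome and its assessment |
| Who checks the diary | The assessors, at each formal visit | Primary outcome and its assessment |
| Outcome visits | Weeks 0, 12, 24, 30 | Primary outcome and its assessment |
| Visits in all | Weeks 0, 4, 8, 12, 16, 20, 24, 30 | Compliance strategy |
| What goes to the assessor | Additional treatments, no timing given | Study medication |
| Where event reports go | E-mail account or telephone line | Study medication |

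All 3 post-baseline outcome visits are among the 8 listed visits, so a diary check falls on each of them. Before the week 24 rating, the assessors will also have checked the diary at weeks 4, 8, 12, 16 and 20. Rating first on the day therefore removes only part of the exposure.

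Two steps are inferences: that the formal visits of one section are the regular visits of the other, and that the diary checkers and the scale raters are the same people. Both are the natural reading, since one term is used and no other raters are described.

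**2. Size under stated assumptions**

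From the article: threshold 4 points, 20 patients per arm. One patient is 1/20 = 5 percentage points.

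Assumed: ADAS-cog change, counted in the direction of improvement, is normal with true mean 0 and SD 5 to 7. The rater adds a shift s of 1 or 2 points. The apparent response rate is P(change ≥ 4) = 1 − Φ((4 − s)/SD).

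| SD | s = 0 | s = 1 | s = 2 | Rise, s = 1 | Rise, s = 2 |
|---|---|---|---|---|---|
| 5 | 21.2% | 27.4% | 34.5% | 6.2 | 13.3 |
| 6 | 25.2% | 30.9% | 36.9% | 5.6 | 11.7 |
| 7 | 28.4% | 33.4% | 38.8% | 5.0 | 10.4 |

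Rises are in percentage points, taken from unrounded rates. They become the difference between arms only if every DTD patient and no placebo patient receives the shift.

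Suppose instead that the shift is added whenever the rater believes that the patient is on DTD, and that beliefs are right with probability p in each arm. The shift then reaches a fraction p of DTD patients and 1 − p of placebo patients, so the arm difference is (2p − 1) times the rise:

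- p = 1: 5.0 to 13.3 points, or 1.0 to 2.7 patients of 20.
- p = 0.6: 0.2 × 5.0 = 1.0 to 0.2 × 13.3 = 2.7 points, or about 0.2 to 0.5 of a patient.
- p = 0.5: zero.

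**The case against.** A reader might infer that assessors receive the adverse-event reports at the rating visits. The article does not say so. Event reports go to the e-mail account or telephone line. What must reach the assessor is, on the plain reading, the additional treatments, with no visit timing. Nobody is named for safety assessment.

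A reader might also infer that the diary unmasks the arm. That is not supported either. The products look and smell alike, patients are masked, and no DTD-specific side effect is described. The diary can suggest the arm, no more.

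The caregiver's opinion is a weaker route than it seems. With masked patients and no true effect, reports of better or worse have no reason to differ by arm. They would add noise and not bias. Under no effect, only differing tolerability could align with treatment, and the article gives no evidence on that. If DTD does have an effect, both routes can align with treatment and inflate it.

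Finally, a journal article need not give the order of procedures within a visit, and a fuller protocol may separate the tasks. This counts against treating silence about order as a fault in itself. It does not answer the point, because the article is not silent: it assigns the diary check and the treatment reports to the assessors. The objections limit the wording and the size, and they leave the exposure in place.

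**Conclusion.** The point holds in a limited form. People who are to be blind, and who are the only outcome raters described, are assigned information at every post-baseline outcome visit that can suggest the arm. The blind is not shown to be broken.

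The 5 to 13 percentage points are an upper bound for an assumed 1 to 2 point shift in favour of patients believed to be on DTD. They rest on perfect guessing, SD 5 to 7 and no true effect. With modest guessing the effect is 1 to 3 points, below one patient per arm. The size is therefore uncertain and may be small, but the risk is avoidable at little cost, and the change should be made.

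The point is separate from the handling of the sealed envelopes, which *Randomization and masking* also gives to the assessors. Moving the envelopes would leave this exposure as it is.

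**What to change.** - In *Primary outcome and its assessment*, state that ADAS-cog, C-MMSE and C-DAD are completed before the rater sees the diary, returned packages or treatment reports.
- In the same section, assign diary checking and package counts to an existing team member who does not rate that patient. This is needed as well as rating first, because diaries are also checked at the earlier visits. *Recruitment procedures* gives the principal investigator and a research assistant assessment duties, so the text should define the person by not rating that patient and not by job title alone.
- In *Study medication*, direct reports of additional treatments to that non-rating team member.

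The cost is a fixed order of visit procedures and some division of work among existing staff. *Study design* requires renewed ethics approval for any amendment. *Trial status* reports 36 patients enrolled against a plan of at least 40, so the change mainly protects visits still to come, and ratings before and after it will have been made under different procedures. The procedure used at completed visits should be documented and reported with the results.
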